A randomized controlled trial (RCT) is need to examine the effectiveness of *en_línea* comparing with a standard primary care group therapy and a control group. All conditions will be described later in detail. We hypothesize that *en_línea* group will obtain better or, at least, similar effectiveness results than the standard therapy group, and better results than the control group. The primary aim of the RCT will be determine the effectiveness weight loss and maintenance of *en_línea* with the two comparison groups. The secondary objectives to determine the effectiveness of *en_línea* in comparison with the other conditions will be: a) the adherence to intervention, i.e. website tasks and mobile application records; b) number and stage of drop outs. We will conduct a 17 weeks, parallel-group, randomized controlled trial. Randomization will be performed with a simple randomization with a 1:1:1 allocation ratio. The aims of this paper are to describe the development of *en_línea* program and the protocol for the RCT.

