#### Standard group therapy

Participants in this arm will received a 10 sessions of standard primary care group therapy. Sessions 1 and 2 will be weekly and sessions from 3 to 10 will be biweekly. Sessions, between 8 and 10 participants, will be conducted by a specialized psychologist and they will last 90 min. Treatment areas will be the same as *en*_*línea,* beginning with nutrition and exercise and a progressive incorporation of the other topics. Material to work at home and self-recording will be provided in paper. The structure of the sessions will be: home activities and self-recording review, new information and strategies, and establishment of activities for the week. Anthropometric measures will be taken at the same time as *en_línea.*

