#### Control group

Participants in the control group only will receive a biweekly newsletter by email without feedback. They will be provided with material and instructions to self-record their daily meals and exercise. The newsletter only will content basic information about nutrition and exercise.

Follow-up sessions will take place in three arms to assess the adherence to the interventions and to evaluate the main objective of this study, the acquirement of long-term healthy habits. These face-to-face sessions will last between 15 and 30 min and will take place 1, 3, 6 and 12 months after the post treatment session. In this follow-ups, we will review: anthropometric measures, quality of life, nutrition and exercise habits.

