#### Secondary outcomes measures

To determine the effectiveness of the different interventions following results will be considered for each intervention arm: 1) Adherence: at least 80% of completed website activities and 80% of self-records; 2) Drop out: Participants must finish the treatment; 3) Quality of life: significant differences between pre-post and follow-ups measures. Moreover, significant differences between the three interventions for the three variables aforementioned.

At the end of the study, participants will receive an email with a satisfaction questionnaire with the website and the mobile application, with an available space to make improvement suggestions.

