### Statistical analysis

To estimate the sample size has been used the primary outcome, weight loss differences between baseline and post-treatment measures. The range of the effect size of the intervention will be 0.5 SD in group comparisons, alpha 5% and two-tail tests [51]. These data determine that we need at least 88 patients per group, considering an expected 31% dropout rate [52], our final choice will be *N* = 305 [53].

Analysis will be performed using STATA/IC 14.2. All data will be checked for missing values, accuracy and normality criteria. Intention to treat analysis (ITT) will be used to analyze the data, including all randomized participants. After that, per protocol analysis will be performed for participants who have completed 17 weeks follow-up. ANOVA for repeated measures, with type of intervention as independent variable and time (baseline and follow-up visits) as dependent variable, will be conducted to analyze primary and secondary outcomes.

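### The adherence outcome depends on a website that two of the three arms never receive, so the planned three-arm comparison is uninformative, and repeated-measures ANOVA does not fit adherence or dropout

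*Protocol article*

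**What the plan says.** **Definition.** Under Secondary outcomes measures, the Protocol article lists adherence, dropout and quality of life, saying that the "following results will be considered for each intervention arm". Adherence is given as "Adherence: at least 80% of completed website activities and 80% of self-records". Dropout is defined by whether the participant finishes the treatment. The paragraph then adds: "Moreover, significant differences between the three interventions for the three variables aforementioned".

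**Objectives.** The last paragraph of the Background names two secondary objectives, both framed as comparisons of en_línea with the other conditions: "the adherence to intervention, i.e. website tasks and mobile application records; b) number and stage of drop outs".

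**What each arm receives.** The en_línea section describes a website with 17 weekly sessions and a mobile application made only for that programme. Under Standard group therapy there are 10 in-person sessions, and "Material to work at home and self-recording will be provided in paper". Control participants "only will receive a biweekly newsletter by email without feedback", plus material to record meals and exercise. The Control group section also says that follow-up sessions in all three arms will assess adherence.

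**Analysis.** The Statistical analysis section names one method, a repeated-measures ANOVA by intervention and time (baseline and follow-up visits), and says it "will be conducted to analyze primary and secondary outcomes". No exception is made for adherence or dropout.

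**The concern.** Half of the adherence definition, the website activities, exists in one arm only. The Background narrows the other half to application records, which also exist only in en_línea. Attendance at group sessions counts for nothing under this wording, and no arm-specific alternative is offered. Yet adherence is to be assessed in each arm and tested between the three.

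This matters because adherence and dropout are the only two secondary objectives the Background names. Poor adherence to web programmes is part of the stated motivation for the trial, and the Discussion expects en_línea to do better on it. An adherence advantage would therefore be a prominent claim. If the definition is followed as written, that advantage could come from the wording alone.

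The second problem is the method. Repeated-measures ANOVA over baseline and follow-up visits needs a quantity with a value at baseline. Whether someone reached an 80% threshold during treatment, or left the trial, has none.

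**Working it through.** The plan gives no adherence figure to reproduce, so the main check sets its sections side by side.

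**Step 1. Can each arm meet the definition?**

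| Component | en_línea | Group therapy | Control |
|---|---|---|---|
| Website activities | yes | none described | none described |
| Application records (Background wording) | yes | none described | none described |
| Self-records in any form | yes, application | yes, paper | material provided; return not stated |
| Stated minimum number of records | yes (at least five meal records a day, daily steps, weekly weight) | not stated | not stated |

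The two 80% thresholds are joined by 'and'. If both must be met, a group-therapy participant who attends all 10 sessions and returns every paper record is still non-adherent. Adherence is then 0% in two arms by construction. If the website part is instead treated as not applicable, the outcome as defined has no value in those arms. Neither reading supports the planned three-arm test. Only self-records in any form are common to all arms.

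**Step 2. How little would it take to produce a significant result? (illustration)**

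Inputs: N = 305 and 31% dropout, both from Statistical analysis; 1:1:1 allocation from Randomization and blinding. Assumption: the comparator arm is coded as zero adherent.

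- Per arm randomised: 305 / 3 = 101.7, about 102.
- Per arm after dropout: 305 × 0.69 / 3 = 70.15, about 70.

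For k adherent of n against 0 of n, the two-sided Fisher p is 2 × C(n, k) / C(2n, k).

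| n per arm | k = 5 | k = 6 |
|---|---|---|
| 102 | p = 0.059 | p = 0.029 |
| 70 | p = 0.058 | p = 0.028 |

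Six adherent en_línea participants are enough: 6/102 = 5.9%, or 6/70 = 8.6%. With assumed true en_línea adherence of 30%, 50% or 70% and about 0% in the comparator, a two-sided 5% test has power above 99.9% at both 88 and 70 per arm. The test would be significant whatever participants in the other arms actually did.

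**Step 3. Does the stated method fit?**

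| Secondary outcome | Type as defined | Baseline value? | Repeated-measures ANOVA |
|---|---|---|---|
| Adherence | threshold met or not | no | does not fit |
| Dropout | finished or not, plus its stage (Background) | no | does not fit |
| Quality of life | score measured before, after and at follow-up | yes | conventional choice |

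**Step 4. Is there a common completion criterion for dropout?**

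Yes. Statistical analysis defines the per-protocol set by completion of the 17-week follow-up, which can be applied to any arm. One gap remains: the Procedure section schedules the week 8 and week 17 meetings for en_línea and the group intervention and does not mention control. The three-arm comparison of post-treatment weight presupposes that control participants are measured then.

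**The case against.** The best defence is that the two 80% thresholds need not form one composite. Self-recording exists in all arms, so that part can be compared, and a sensible analyst would treat the website part as not applicable rather than failed. This stands in part. A rate of exactly 0% is one reading, and 'undefined' is the other. It does not rescue the plan, because the text asks for a three-arm comparison of adherence as defined and the Background ties the records to the application.

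A second defence is that choosing between logistic regression and time-to-event methods is usual SAP detail. That is true of an open choice. Here the article names one method for every secondary outcome, and it does not fit two of them.

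A reader might also infer more than the documents support:

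- *That any true en_línea rate above 6–7% would be significant.* The Fisher threshold is an observed count. With 102 per arm, the chance of observing at least 6 is about 58% at a true rate of 6%, 73% at 7% and 95% at 10%.
- *That dropout has no meaning in a newsletter-only arm.* The interventions last 17 weeks, control participants have follow-up sessions, and the 17-week completion criterion applies to them. The dropout wording is terse, not empty.
- *That adherence is never measured repeatedly.* Records are daily and weekly, and follow-up sessions are said to assess adherence. The sound objection is the missing baseline value and the yes/no form.
- *That the data for a repair are already collected.* Records are reviewed in group sessions, but the article does not say that attendance is logged or that control participants return their records.

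**Conclusion.** The point holds for the adherence definition and for the analysis method. As written, the between-arm adherence comparison is either fixed by the definition or undefined in two of three arms, and it cannot inform the objective it serves. The 6/102 figure only illustrates how easily a significant result would follow. It rests on equal arms of about 102 and on coding participants without website access as non-adherent.

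The ANOVA mismatch is subsidiary but real. It applies to threshold adherence and dropout, not to weight or quality of life.

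This should be fixed, but it is not a flaw in the trial's primary question: primary weight loss, quality of life and sample size are untouched. The article says that recruitment is under way and no analysis has been done, so the definition can still be changed without knowledge of results.

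**What to change.** 1. Report website-activity adherence in en_línea only, descriptively.
2. Base the three-arm comparison on the self-record component. State the same denominator for all arms, and require paper and control records to be returned and counted.
3. Optionally, compare the two active arms on the share of each arm's own scheduled sessions or activities completed, with group attendance logged.
4. Define dropout identically in all arms as not completing the 17-week follow-up, the criterion already used for the per-protocol set. State that control participants attend that visit, and record when each dropout occurs.
5. Analyse adherence and dropout as proportions (logistic regression, or risk difference with 95% CI) and stage of dropout as time to event. Keep the repeated-measures model for weight and quality of life.

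The cost is a wording change plus a small amount of extra record collection and attendance logging, mainly in the control and group arms. The adherence claim available to en_línea becomes narrower.

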### Study design and randomization

#### Procedure

Participants will be recruited through advertising (flyers, posters, University website, workplace-based emails and social networks). Obese and overweight people interested in participating in the study must send an email to the coordinator of the project. Participants will receive an email to attend an appointment with a psychologist. In this first appointment, patients will be informed about the aims and characteristics of the study, they must sign the written informed consent and, after that, a brief interview and baseline anthropometric measures will be taken. Anthropometric measures will be weight, height; and, neck, chest, waist, hips, leg and arm circumferences. All measures will be taken with the participant wearing light clothing and without shoes. Height will be taken with 1 cm using a stadiometer. Weight will be measured on a digital scale. Circumferences measurements will be measure following the indications provided by WHO [33].

To ensure the accomplishment of inclusion and exclusion criteria participants must answer a large battery of questionnaires specified later. These questionnaires are divided in two batches. After the first in-person appointment, participants will receive an email with the instructions to complete the first batch of questionnaires, they will be provided with an identity number for data protection and with the direct link to the available questionnaires in the platform SurveyMonkey. After the completion of the first part, a second email with the link to the second batch of questionnaires will be sent.

Assessment phase will last 2 weeks, selected participants will be randomized to one of the three study arms. Patients will receive an email with information about their belonging group. Obese and overweight people randomized to *“en_línea”* program, must assist to a 1 h training session to get familiar with the website and the mobile application. When participants are included in the study, both *en_línea* and group intervention, they will be given timings for follow-up meetings during the treatment at week 8 and week 17. After interventions finish, follow-up meetings will be happened at 1, 3, 6 and 12 months. In the follow-up visits a brief interview and anthropometric measures will be taken again, the duration of these meeting will be between 15 and 30 min (Fig. 3).

**Fig. 3 Fig3:**
[figure not shown]
Flow diagram of *en_línea* study

The first evaluation and follow-up visits will be conducted by the coordinator of the project and the interventions will be conducted by two psychologists. The psychologists involved are all certified general sanitary psychologist training for the interventions chosen for this investigation.

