### Outcomes

#### Primary outcomes measures

The primary outcome is the weight loss. First, differences between the pre and post measures for each treatment arm. Treatment success is defined as 5–10% of weight loss respect the initial weight. Then, significant differences in weight loss and other anthropometric measures, specified later, between the three treatment arms. Finally, the maintenance of weight loss during the follow-ups, significant differences between the three treatment arms.

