#### Randomization and blinding

Simple randomization will be applied using computer-generated random numbers [34], with a 1:1:1 allocation ratio. Simple randomization has proven to be reliable to large clinical research, generating similar numbers of subjects per group [34]. Participants will be randomly assigned to *en_línea* program, standard group therapy or control group. Randomization will be carried out by an independent researcher of the study. Therapists will not know the patient allocation until the coordinator inform them to begin the treatment. Thus, blinding will not be possible for the therapists during the intervention.

Currently, this study is in the recruitment phase. No statistical analysis have been performed at this time.

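### The coordinator who relays allocation also retakes the anthropometry after baseline, which exposes the tape-measured circumferences to avoidable detection bias

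*Protocol article*

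**What the plan says.** Four places in the protocol article bear on this point.

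- **Who measures.** The text after Fig. 3 states: "The first evaluation and follow-up visits will be conducted by the coordinator of the project". Procedure adds: "In the follow-up visits a brief interview and anthropometric measures will be taken again". It applies the same label to the on-treatment and end-of-treatment visits of the two active arms: "they will be given timings for follow-up meetings during the treatment at week 8 and week 17".
- **Who holds the allocation.** Randomization and blinding states: "Randomization will be carried out by an independent researcher of the study". It then says: "Therapists will not know the patient allocation until the coordinator inform them to begin the treatment".
- **What is said on blinding.** The one explicit statement concerns the therapists: "Thus, blinding will not be possible for the therapists during the intervention". The article says nothing about masking the person who measures.
- **What is measured.** Primary outcomes measures names weight loss as the primary outcome, then lists under the same heading "significant differences in weight loss and other anthropometric measures, specified later, between the three treatment arms". Procedure specifies these measures as weight, height and "neck, chest, waist, hips, leg and arm circumferences". Weight is read from a digital scale, and circumferences follow WHO indications.

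**The concern.** Two tasks that are best kept apart are assigned to one person. The coordinator knows each participant's arm by the time treatment starts, and later takes the measurements that are compared between arms. Tape readings depend on placement and tension, so a measurer who knows the arm can shift them without intending to. The team is testing its own programme, and the Background section states a hypothesis in its favour.

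A shift that differs between arms goes directly into the between-arm contrast. The repeated-measures ANOVA cannot separate it from a treatment effect. The per-protocol analysis would carry the same shift.

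The arrangement is expressly stated, so it is not a detail that a condensed article has left to the full protocol. It is also at least partly avoidable, because someone outside the coordinator's role already produces the allocation.

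**Working it through.** The plan gives no figure for measurement bias, so there is none to reproduce. The check is mainly a reading of the sections together, followed by an illustration of scale.

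**Step 1: does the measurer know the arm?** The coordinator informs the therapists of the allocation when treatment is to begin (Randomization and blinding), so the coordinator has it from then at the latest. The coordinator conducts the follow-up visits (text after Fig. 3), where anthropometry is repeated (Procedure). For the visits at 1, 3, 6 and 12 months this follows directly. For weeks 8 and 17 it rests on Procedure calling them follow-up meetings. The Abstract and the paragraph closing the Control group section count follow-ups only from the post-treatment appointment, so the coordinator's role at week 17 is a reasonable inference and not an express statement.

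**Step 2: which measures are exposed?**

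| Measure | Source in the article | Exposure to a measurer who knows the arm |
|---|---|---|
| Baseline anthropometry | First appointment, before randomisation | None |
| Post-baseline weight | Digital scale, light clothing, no shoes | Small |
| Post-baseline circumferences (six) | Tape, WHO indications | Main exposure |
| SF-36 | Respondent questionnaire | Not assessor-read |
| Adherence | Website activities and self-records | Not assessor-read |
| Drop-out | Treatment completion | Not assessor-read |

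**Step 3: what could a shift do?** Assume no true difference between two arms and a differential reading shift of b standard deviations. With n per arm, the two-sided 5% test then rejects with probability

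Φ(b/√(2/n) − 1.96) + Φ(−b/√(2/n) − 1.96).

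Two values of n come from Statistical analysis. Applying 31% dropout to N = 305 gives 305 × 0.69 / 3 = 70.15, or about 70 per arm. The second value is the stated 88 per group. (The two do not agree, which is a separate matter.)

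Example with n = 70 and b = 0.1: √(2/70) = 0.169 and 0.1/0.169 = 0.592. Then Φ(−1.368) + Φ(−2.552) = 0.0856 + 0.0054 = 0.091.

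| Assumed shift b | n = 70 per arm | n = 88 per arm |
|---|---|---|
| 0 | 5.0% | 5.0% |
| 0.05 SD | 6.0% | 6.3% |
| 0.10 SD | 9.1% | 10.2% |
| 0.20 SD | 21.9% | 26.4% |

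If the SD of change in waist were 5 cm (also an assumption), 0.1 and 0.2 SD would be 0.5 and 1 cm on the tape. The table describes a hypothetical bias in a circumference. It does not describe scale weight.

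**The case against.** The strongest reply is that the trial's main claim rests on weight. Primary outcomes measures opens with weight loss, the Abstract names only weight loss and its maintenance, treatment success is a percentage of initial weight, and the sample size uses weight. A digital scale leaves little to the measurer. The article also sets uniform clothing conditions, cites WHO indications for the tape, and keeps the measurer separate from the two treating psychologists. All of this stands, and it confines the concern mainly to the circumferences. It does not remove it: standard technique is not masking, and the circumferences are listed under the primary outcome heading.

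A second reply is that masking cannot last. The Control group section says that follow-up sessions serve partly to assess adherence and to review habits. Adherence means different things in each arm, so the interviewer will often learn the arm, and the same coordinator returns at later visits. This also stands. Masking through to data lock is not realistic, and the remedy can only be partial.

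A third reply is that the error rates above would apply to any open trial of this size. That is correct; they show scale and do not demonstrate bias in this trial.

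A reader might also infer three stronger things that the article does not support:

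- **That every outcome is measured unblinded.** The table in Step 2 shows otherwise.
- **That allocation concealment is broken.** The first evaluation precedes randomisation, and an independent researcher carries randomisation out.
- **That the coordinator sends participants their group.** Procedure does not name the sender of those emails; only the notice to therapists is said to pass through the coordinator.

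**Conclusion.** The point holds within limits. One person both relays the allocation and retakes anthropometry after baseline, and the article gives no reason why the measurer must know the arm. The resulting risk of detection bias is mainly a matter for the six circumferences. The weight result is not invalidated by this arrangement.

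The size is unknown. Under assumed shifts of 0.1 and 0.2 SD with 70 per arm, a nominal 5% error rate would be about 9% and 22%. The conclusion rests on reading weeks 8 and 17 as coordinator visits for the on-treatment and post-treatment measurements; it needs no such reading for the 1 to 12 month visits. A modest, inexpensive change is worth making.

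**What to change.** 1. For participants not yet allocated, have the independent researcher who randomises send the allocation directly to the therapists, and keep the coordinator off the allocation list. Recruitment is under way, so participants whose arm the coordinator already knows stay unmasked.
2. At each post-baseline visit, take weight and circumferences before the interview, with earlier values not visible to the measurer. Record any unmasking and when it occurred.
3. State in Randomization and blinding that assessor masking is only partial, because the same visits review adherence.
4. In Primary outcomes measures, rest the primary conclusion on scale weight and report the circumferences as possibly influenced by the assessor.

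The cost is a small change in workflow and some added wording; no extra assessor is needed. The drawback is incomplete masking, especially after the first post-baseline interview.
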